**Fig. 1 Fig1:**
[figure not shown]
Study Design

### Measures

Participants will be invited to the study center to complete baseline (T0) and follow-up assessments (T1). At the study center, participants will undergo different anthropometric, physical, motor and cognitive tests, as well as an assessment of motivational stages to engage in PA. Cardiovascular fitness will be assessed using the 2-min step test [30]. Functional status and physical performance will be measured employing the Short Physical Performance Battery (SPPB) which includes balance, gait speed, and chair raising tests [31]. Moreover, postural control under dynamic conditions [32], strength of the upper extremities [33], hand grip strength [34], height, weight, and body fat will be assessed using stadiometers and bioimpedance scales. Cognitive dysfunction [35], memory (Verbal Learning and Memory Test (VLMT), [36]), and attention and inhibition (Simon Task, [37]) will be assessed in cognitive tests. In addition, working memory updating and inhibition (Random Number Generation Test (RNGT), [38]), and postural control under static conditions (measure of tandem stand by use of iPad, software: Sensor Data, Wavefront Labs, [39]) will be assessed under single- and dual-task conditions. Motivational stages regarding PA will be measured via a validated algorithm [40, 41].

After both assessments, all participants will receive an accelerometer (ActiGraph GT3x+) to objectively measure PA and a self-administered questionnaire. Participants will be instructed to wear the accelerometer on the right hip and during the day for seven days following baseline and follow-up assessments. The self-administered questionnaire will contain validated instruments and self-generated items assessing levels of PA, perceived physical environment, social support, health behavior, quality of life, and previous experience with using technology (for further detail on the instruments included in the questionnaire, see Table 1). Sociodemographic information will include age, gender, migration background, education, employment, and household income. In addition, participants of intervention groups 1 and 2 will fill out a self-administered questionnaire at the follow-up comprised of self-generated items regarding use and acceptance of the website, attendance of the offered group sessions, and overall satisfaction with the interventions.

**Table 1 Tab1:** Measures in the self-administered study questionnaire

Outcome measure	Instrument/scale
Physical activity	
Physical activity	International Physical Activity Questionnaire (IPAQ) [49]
Intention to engage in physical activity	Health Action Process Approach (HAPA), intention [40, 41]
Self-efficacy regarding physical activity	HAPA, self-efficacy [40, 41]
Planning for physical activity	HAPA, planning [40, 41]
Physical self description	Physical self-description (PSDQ) [50]
Physical environment	
Physical activity and neighborhood environment	International Physical Activity Questionnaire Environmental module (IPAQ-E) [51]
Social support, social activities	
Social support for engaging in physical activity	Social support and exercise survey (modified, [40, 41])
Social networks	Self-generated items
Social activities	Florida Cognitive Activities Scale (modified, [52, 53])
Health behavior	
Subjective age	Self-generated item
Health-related quality of life	Short-Form (SF)-12, only 1 item [54]
Objective health	Diseases and medication use (modified, [55])
Risk perception	Berlin Risk Appraisal and Health Motivation Study (BRAHMS) [56]
Falls	Elderly Fall Screening Test (EFST) (modified, [57])
Fear of falling	Geriatric Fear of Falling Measurement (GFFM) [58]
Diet	Food Frequency Questionnaire [59]
Alcohol consumption	Alcohol Use Disorders Identification Test Short Version (AUDIT-C) [60]
Smoking behavior	Smoking Behavior Questionnaire [61]
Stage assessment of smoking behavior, alcohol consumption, fruits and vegetable consumption	Stage assessment [40, 41]
Quality of life and well-being	
Quality of life	Satisfaction with Life Scale (SWLS) [62]
Emotional well-being	Self-generated items
Depression	Centers for Epidemiologic Studies Depression Scale (CES-D) [63]
Personality	NEO Five Factor Inventory (NEO-FFI) [64]
Previous experiences with technology	
Use of computers/smartphones/applications	Self-generated items
Technology commitment	Technology Commitment Scale [65]
Use, acceptance, and satisfaction with interventions	
Use and acceptance of various components of the website, attendance of the offered group sessions, and overall satisfaction with the interventions	Self-generated items

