### Study aims

The following main research question will be examined in this study:Is a web-based intervention with subjective and objective PA monitoring more effective for the promotion of PA among older adults than a web-based intervention with subjective PA monitoring only compared to a delayed intervention control group?

Secondary research questions of the study are the following:Do participants’ characteristics (e.g., age, gender, motivational stage) influence intervention attendance and PA behavior?Is participation in the web-based interventions associated with improvements in secondary outcomes, such as well-being, quality of life, fear of falling, physical and cognitive functioning?

An additional objective of the study is to improve our understanding of how web-based interventions and technologies for PA tracking ought to be designed to be usable for the target group and which features ought to be included from the user’s point of view.

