### Interventions

Two web-based interventions promoting self-monitoring of PA will be developed. Both will be based on self-regulation theory [42, 43] and on principles of behavior change (e.g., shaping knowledge, feedback and monitoring, goals and planning, social support, comparison of behavior, rewards, [44]). Participants in the intervention groups will receive brochures with PA recommendations including exercises to improve balance (two times per week), strength (on two or more nonconsecutive days per week involving major muscle groups), and endurance (for at least 150 min with moderate intensity or at least 75 min with vigorous intensity each week in bouts of 10 min, or an appropriate combination of both types of activities), according to the recommendations of the WHO and the ACSM. Depending on PA-level assessed at baseline and gender, participants will be provided with different brochures outlining exercises for different levels of difficulty and displaying pictures of male vs. female older adults modeling the exercises.

In the first intervention arm (intervention group 1), participants will receive access to a web-based PA diary and will be encouraged to track their behavior over a 10-week period. Participants in the second intervention arm (intervention group 2) will additionally receive Fitbit Zips (Fitbit, San Francisco, USA) to objectively track PA; data of the Fitbit Zips will be synchronized with the website following regular time intervals. The website will provide weekly feedback on whether PA goals (WHO recommendations for moderate exercise time, flexibility and strength training) are reached (and goal-specific rewards), and will provide opportunities to network with other intervention participants via an invite friends function and a forum. In addition to the web-based interventions, participants will be offered weekly group meetings in their communities led by trained research assistants. During these 90-min meetings, participants can resolve technical problems with the website, receive health education regarding healthy ageing, and practice PA in groups. All intervention materials (e.g., PA recommendations and instructions) will be tailored to participants’ age, gender, motivation to engage in PA, and PA-level assessed at baseline.

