### Analytic strategy

#### Quantitative analysis, sample size

Hierarchical linear regression models will be used to analyze the intervention effects. Due to the week-wise randomization scheme, recruitment week will be included as a clustering variable. Change over time in objectively measured PA will serve as the primary outcome variable. Change over time will be calculated by subtracting the baseline value from the follow-up value (PA_T1_-PA_T0_). To assess the intervention effects, two dummy variables for intervention groups 1 and 2 will be added contrasting the change over time in PA in each intervention arm with the changes in the delayed intervention control group. Expecting small to moderate intervention effects [45], we calculated the sample size assuming a standardized mean difference of 0.33 in change over time between the intervention groups and the delayed intervention control group. Further, assuming ten clusters (recruitment weeks) per study arm and an intraclass correlation of 0.01, 190 participants per study arm will be necessary for the analysis with α = 0.05 (two-sided test) and β = 0.20. Expecting a loss to follow-up of 20%, we aim for a sample size of *n* = 684 at baseline.

Changes in cardiovascular fitness, physical performance, body fat, cognitive dysfunction, fear of falling, and quality of life will be analyzed as secondary outcomes. Several variables will be included as potential confounders, such as baseline PA-level, age, gender, education, motivational stage, and other health behaviors. In additional analyses, the moderating influence of gender, socioeconomic strata, and motivational stage on intervention effects will be explored.

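### The only stated measure of intervention attendance, an outcome of the first secondary question, is self-report at the 12-week follow-up, which participants lost by then will not supply

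*Protocol article*

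**What the plan says.** - **The question.** Under Study aims, the first secondary question asks whether characteristics such as age, gender and motivational stage "influence intervention attendance and PA behavior". Attendance is therefore one of its two outcomes.
- **The measure.** Under Measures: "participants of intervention groups 1 and 2 will fill out a self-administered questionnaire at the follow-up comprised of self-generated items regarding use and acceptance". The same sentence extends the content to "attendance of the offered group sessions, and overall satisfaction with the interventions". Table 1 repeats this, listing "Use and acceptance of various components of the website, attendance of the offered group sessions, and overall satisfaction with the interventions" with self-generated items as the instrument. No other source for attendance is named.
- **Records the intervention could produce.** The Interventions section says that "participants will receive access to a web-based PA diary and will be encouraged to track their behavior over a 10-week period", that "data of the Fitbit Zips will be synchronized with the website following regular time intervals", and that "participants will be offered weekly group meetings in their communities led by trained research assistants". It also describes an introductory group session and a second group meeting five weeks into the intervention. None of these is named as a measure of attendance or use.
- **Expected loss.** Under Quantitative analysis, sample size: "Expecting a loss to follow-up of 20" per cent, with 684 participants planned at baseline.

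**The concern.** An attendance item asked once, at the end, is unavailable for anyone who does not reach the end. If people who attended little are also less likely to return, the missing values depend on the outcome itself. Those who do return must reconstruct about ten weeks of meetings from memory.

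Two results could suffer. The level of attendance would read too high. The association between attendance and motivational stage could be distorted if stage also affects who is lost. Both can be avoided at little cost, because staff lead the meetings and see who comes.

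**Working it through.** **Inputs from the article:** 190 analysable participants per arm, three arms, 20% loss, 684 at baseline. The article gives no attendance rates and no pattern of loss, so every rate below is an assumption.

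**The article's own figure.** 3 × 190 = 570, and 570 × 1.2 = 684, which is the stated baseline number. Per arm, 684 / 3 = 228. Groups 1 and 2 together are 2 × 228 = 456.

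**Participants without attendance data if the questionnaire is the source.** At the stated 20% loss, 456 × 0.20 = 91.2, about 91. If 190 per arm were in fact retained (a loss of 38 / 228 = 16.7%), the number is 2 × 38 = 76.

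**Effect on mean attendance.** Let c be the mean share of sessions attended by completers and d the share attended by those lost. With 20% lost, the true mean is 0.8c + 0.2d, so the completer mean is too high by 0.2(c − d).
- c = 50%, d = 40%: 0.2 × 10 = 2 points.
- c = 70%, d = 0%: 0.2 × 70 = 14 points.
- c = d: no bias.

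**Effect on the association, loss depending on attendance only.** Assume two motivational stages of equal size, with good attendance in 40% of the low stage and 60% of the high stage (50% overall). Loss is 5% in attenders and 35% in non-attenders (20% overall).
- Low stage: 0.40 × 0.95 = 0.38 attenders and 0.60 × 0.65 = 0.39 non-attenders remain; 0.38 / 0.77 = 49.4%.
- High stage: 0.60 × 0.95 = 0.57 and 0.40 × 0.65 = 0.26 remain; 0.57 / 0.83 = 68.7%.
- Overall: (0.50 × 0.95) / 0.80 = 0.475 / 0.80 = 59.4%, against a true 50%.
- The difference is 19 points, against a true 20.
- Odds ratio, true: (0.60/0.40) / (0.40/0.60) = 2.25. In completers: (0.57/0.26) / (0.38/0.39) = 2.25, unchanged.

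**Effect on the association, loss also depending on stage.** Keep 5% loss in attenders, but let loss be 50% in low-stage and 15% in high-stage non-attenders.
- Low stage: 0.38 / (0.38 + 0.60 × 0.50) = 0.38 / 0.68 = 55.9%.
- High stage: 0.57 / (0.57 + 0.40 × 0.85) = 0.57 / 0.91 = 62.6%.
- Overall loss: (0.32 + 0.09) / 2 = 20.5%.
- The difference falls from 20 points to about 7.

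The level is biased whenever those lost attended less. The association is biased materially only in the second pattern.

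**The case against.** The strongest reply is that the article is a condensed document. It does not say that the questionnaire is the sole source or that registers and logs will not be kept, and such operational detail often sits in the full protocol. For website use, weekly feedback on goals and Fitbit synchronisation imply that individual records exist. This stands as a limit: the questionnaire is the only stated source, not demonstrably the only one. It does not dispose of the point, because the article does not leave the attendance measure open. It gives the instrument, the respondents and the timing, and Table 1 repeats the instrument.

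Four stronger readings are tempting, and the article does not support them.
- **That stopping attendance and leaving the study are the same event.** The weekly meetings are an offer, and follow-up is a separate visit to the study center. Someone can skip every meeting, return, and report zero sessions. A link is plausible but not documented.
- **That the effect of motivational stage will be masked.** The fall from 20 points to 7 needs loss among non-attenders to differ sharply by stage. If loss depends on attendance alone, the odds ratio does not move.
- **That website use is also an outcome of this question.** Study aims names attendance and physical activity. Use appears only in Measures and Table 1.
- **That reported acceptance is overstated.** Acceptance comes from those who complete follow-up, but the direction of any bias is not known, and attendance registers would not repair it. The focus groups on group 2 usability add user evidence, though they do not recover participants who were lost.

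**Conclusion.** The point holds as a weakness in a stated measurement choice for one outcome of one secondary question. If the follow-up questionnaire is the source used, attendance is missing for about 91 of 456 participants in groups 1 and 2 (76 if 190 per arm are retained) and relies on recall for the others. Mean attendance would be overstated by 2 to 14 points under the assumed ranges when those lost attended less, and by nothing when they attended equally. Distortion of the association with participant characteristics is possible, but it needs loss to depend on stage as well as attendance. The primary outcome, change in objectively measured physical activity, is unaffected. This is a cheap improvement to a secondary outcome and does not threaten the trial's main conclusion.

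**What to change.** - Take attendance, for every participant allocated to groups 1 and 2, from registers kept by the research assistants at the weekly, introductory and week-5 meetings. Use these registers as the attendance outcome for the first secondary question, and count dropouts by their recorded attendance.
- Take website and Fitbit use from diary-entry, log-in and synchronisation records.
- Keep the follow-up questionnaire for acceptance and satisfaction, and report those as results in completers only.
- If the full protocol already provides for registers and logs, name them in the description of measures as the source.

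The cost is a sign-in sheet at meetings that are already staffed, some data entry and record export, and a line in the consent text on log data. The registers must be in place before the first meeting, because attendance cannot be reliably reconstructed afterwards.

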### Interventions

Two web-based interventions promoting self-monitoring of PA will be developed. Both will be based on self-regulation theory [42, 43] and on principles of behavior change (e.g., shaping knowledge, feedback and monitoring, goals and planning, social support, comparison of behavior, rewards, [44]). Participants in the intervention groups will receive brochures with PA recommendations including exercises to improve balance (two times per week), strength (on two or more nonconsecutive days per week involving major muscle groups), and endurance (for at least 150 min with moderate intensity or at least 75 min with vigorous intensity each week in bouts of 10 min, or an appropriate combination of both types of activities), according to the recommendations of the WHO and the ACSM. Depending on PA-level assessed at baseline and gender, participants will be provided with different brochures outlining exercises for different levels of difficulty and displaying pictures of male vs. female older adults modeling the exercises.

In the first intervention arm (intervention group 1), participants will receive access to a web-based PA diary and will be encouraged to track their behavior over a 10-week period. Participants in the second intervention arm (intervention group 2) will additionally receive Fitbit Zips (Fitbit, San Francisco, USA) to objectively track PA; data of the Fitbit Zips will be synchronized with the website following regular time intervals. The website will provide weekly feedback on whether PA goals (WHO recommendations for moderate exercise time, flexibility and strength training) are reached (and goal-specific rewards), and will provide opportunities to network with other intervention participants via an invite friends function and a forum. In addition to the web-based interventions, participants will be offered weekly group meetings in their communities led by trained research assistants. During these 90-min meetings, participants can resolve technical problems with the website, receive health education regarding healthy ageing, and practice PA in groups. All intervention materials (e.g., PA recommendations and instructions) will be tailored to participants’ age, gender, motivation to engage in PA, and PA-level assessed at baseline.

One week after the baseline assessment, the intervention will be introduced to participants of intervention groups 1 and 2 separately in group sessions with a maximum of 24 participants. Five weeks after the start of the intervention, a second group meeting will be held to ensure the proper use of the website and the Fitbit Zips in the two intervention groups. After completion of the follow-up assessment, persons in the delayed intervention control group will receive access to the web-based intervention of intervention group 1. However, no weekly group meetings will be offered to participants in this study arm.

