**Methods/Design:**

Study participants will be randomly assigned to one of three study arms in five communities in the Bremen-Oldenburg metropolitan region: a) Participants in the first arm will receive access to a web-based intervention for 10 weeks allowing them to track their weekly PA (subjective self-monitoring, intervention group 1); b) participants in the second arm will receive access to the web-based intervention for 10 weeks and, in addition, track PA using Fitbit Zips (objective self-monitoring, intervention group 2); c) participants in the delayed intervention control group will receive access to the intervention implemented in the first study arm after completion of the 12-week follow-up in the other two groups within each community. In addition, weekly group meetings in the communities will be offered to study participants in the intervention groups providing the opportunity to address questions related to the use of the website and to practice PA in groups (e.g., neighborhood walks, strength and balance exercises). To evaluate short-term effects of the intervention on physical and psychological health, PA, physical fitness, and cognitive and psychological variables will be assessed at baseline and 12-week follow-up.

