#### Inclusion and exclusion criteria

Residents of the five communities will be eligible for study participation if they are between the ages of 65 and 75 years, if they are able to live independently (i.e., in own apartment or room without assisted living, no regular home nursing), and if they provide an informed consent to participate in the study. Further criteria for inclusion in the study are basic knowledge of German, the ability to walk without a walking aid, and to participate in study assessments and weekly group meetings without external support. Also, internet access at home or at family members’ or friends’ houses is a precondition for participation. Participants will be excluded from the study if they have planned a vacation for more than one month during the intervention period, display cognitive impairment (Mini-Mental-Score ≤ 27) or other permanent impairments (e.g., stroke, neurological diseases, such as Parkinson’s) or if there are any medical contraindications regarding program participation.

After successful screening for study eligibility, study participants will be assigned to one of three study arms by the study nurses: a) a web-based intervention with subjective PA self-monitoring (intervention group 1), b) a web-based intervention with subjective and objective PA self-monitoring (intervention group 2) or c) a delayed intervention control group (waitlisted control group) receiving the intervention of intervention group 1 after completion of the 12-week follow-up (see Fig. 1 for the study design). Each intervention condition will be randomly assigned to certain weeks of baseline assessment. Participants will be free to choose from available time slots during a phone call with a study nurse, but only after their decision will they be informed about which intervention condition was assigned to this particular week.

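### The trigger for controls' website access is worded differently in three places, and none of them keeps access out of the controls' own follow-up accelerometer week

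*Protocol article*

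**What the plan says.** The protocol article states the access trigger for the delayed intervention control group three times.

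- Abstract, Methods/Design: "after completion of the 12-week follow-up in the other two groups within each community".
- Inclusion and exclusion criteria: "receiving the intervention of intervention group 1 after completion of the 12-week follow-up", without saying whose follow-up.
- Interventions: "After completion of the follow-up assessment, persons in the delayed intervention control group will receive access to the web-based intervention of intervention group 1". This reads most naturally as the control participant's own assessment.

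The Measures section describes the baseline (T0) and follow-up (T1) assessments as visits to the study centre. It then says "After both assessments, all participants will receive an accelerometer (ActiGraph GT3x+) to objectively measure PA", to be worn "during the day for seven days following baseline and follow-up assessments". The self-administered questionnaire is handed out at the same point.

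Under Quantitative analysis, sample size: "Change over time in objectively measured PA will serve as the primary outcome variable". It is computed as the T1 value minus the T0 value, and each intervention arm is contrasted with the control arm.

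**The concern.** Conditions are randomised to weeks of baseline assessment, so the arms reach follow-up on different calendar dates. A trigger tied to the other arms' follow-up and a trigger tied to a control's own assessment therefore generally give different access dates.

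Neither trigger refers to the seven days in which T1 activity is recorded. The website offers a diary, feedback on goals and rewards, all meant to raise activity. Controls who have it during that week may be more active than untreated controls would be. The same control arm is the comparator for both primary contrasts, so both estimates could be pulled toward zero. Fear of falling and quality of life, which are secondary outcomes measured in the questionnaire handed out after the visit, share the exposure.

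**Working it through.** **1. Interventions wording against the Measures timeline**

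| Step | T0, intervention arms | T1, controls |
|---|---|---|
| Study-centre visit | day 0 | day 0 |
| Accelerometer worn | the 7 days after the visit | the 7 days after the visit |
| Website access | one week after the assessment | after completion of the assessment, no gap stated |
| Wear days that can fall after access | 0 | 0 to 7 |

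The Interventions section introduces the intervention one week after the baseline assessment. There *assessment* means the visit, and the gap leaves the T0 wear week clear. The same section uses the same word for the controls' trigger but gives no gap. If *completion* is meant to include the wear week, the overlap is 0 days. If it means the visit, the overlap can be all 7 days, for any control.

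**2. Abstract wording read alone**

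Controls whose baseline week precedes the community's last intervention week are protected, because their own T1 week is over first. Controls whose baseline week comes after it can get access before or during their own T1. The document does not give the order of weeks, so the exposed share can lie anywhere from none to all of the control weeks.

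One illustrative layout is 10 weeks per arm (from the sample-size section) spread evenly over five communities: 2 control and 4 intervention weeks per community, in unrestricted random order.

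- P(last week is a control week) = 2/6 = 1/3
- P(last two weeks are both control weeks) = 2/6 × 1/5 = 1/15
- Expected exposed control weeks per community = 1/3 + 1/15 = 0.4. Over five communities this is 2 of 10, or 20%.
- P(at least one exposed control week in the trial) = 1 − (2/3)^5 = 0.868

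**3. The plan's power figure**

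Inputs from Quantitative analysis, sample size: d = 0.33, 10 clusters per arm, ICC 0.01, two-sided α = 0.05, power 0.80, 190 per arm.

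- Design effect = 1 + (19 − 1) × 0.01 = 1.18
- n = (t₀.₉₇₅ + t₀.₈₀)² × 2 / 0.33² on 2 × 10 − 2 = 18 df = 161.2, and 161.2 × 1.18 = 190.3. This matches the stated 190.
- Non-central t power with 190 per arm is 0.7996.

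**4. Illustrative dilution**

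Let f be the share of control data exposed and g the share of the full effect that appears in exposed controls within the week. Then d* = 0.33 × (1 − f × g). Neither f nor g is in the document.

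| f | g | d* | Power |
|---|---|---|---|
| any | 0 | 0.330 | 0.80 |
| 0.2 | 0.10 | 0.323 | 0.78 |
| 0.2 | 0.25 | 0.314 | 0.76 |
| 0.2 | 0.50 | 0.297 | 0.71 |
| 1 | 0.10 | 0.297 | 0.71 |
| 1 | 0.20 | 0.264 | 0.61 |
| 1 | 0.30 | 0.231 | 0.50 |

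**The case against.** **The rules do not strictly conflict.** A reader might infer that the sections contradict each other. They do not: each sets a condition of the form *after completion*, two of the three do not say whose follow-up is meant, and waiting for the later date satisfies all of them. Access before a control's own T1 visit then drops out. This stands, and the point is an unreconciled inconsistency. The later date still leaves a gap, however. A control whose own visit is the later event could get access on the first day of the wear week.

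***Completion* may include the wear week.** The abstract lists physical activity among the things assessed at follow-up, and the clear week at baseline suggests that the same was intended at T1. This is a fair reading, and on it there is no overlap. But the Measures section places the wear week after the assessment, and nothing states the intended reading.

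**Any effect within a week may be small.** Exposure during the wear week is at most seven days under the Interventions rule, website feedback is weekly, and controls are offered no weekly group meetings. This stands, and it makes the larger losses in the table hard to defend as expectations.

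**Activation dates are operational detail.** A journal article can leave these to the full protocol. That would answer the point if the article were silent, but it states the trigger three times in wordings that do not agree.

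**Conclusion.** The concern holds as an inconsistency with a risk to the primary outcome. The three access triggers are not aligned, and none protects the controls' T1 accelerometer week. Followed literally, the Interventions wording permits access during that week. The abstract's wording, read alone, permits it even before T1 for control weeks that follow the community's last intervention week.

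A reader might go further and infer that the primary outcome is contaminated, or that a particular loss of power follows. The documents support neither. Staff may wait for the device to come back, and the size of any effect within a week cannot be derived. If there is none, power stays at 80%. A 10% loss of the 0.33 effect would bring it to 71%, as an illustration only. The 20% exposed share and the 87% probability rest on an assumed layout of two weeks per arm per community in unrestricted random order.

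The likely direction is toward no difference, in both contrasts with control. The difference between the two intervention groups would not be affected, because control data cancel out of it.

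**What to change.** Replace the wordings in the abstract, the eligibility section and the Interventions section with one rule that has two conditions, access opening at the later of the two dates:

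1. No control account is activated before that participant's own seven-day T1 accelerometer wear and T1 questionnaire are complete.
2. The abstract's community condition is kept: follow-up in the two intervention groups of that community is complete.

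The second condition should stay. With the first alone, early controls could be active on a site with a forum and an invite-friends function while others in their community are still being followed up.

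Log the activation date for each control, so that any T1 week that overlaps with access can be identified.

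The cost is a change of wording and one logged date. Access for some controls is delayed, by about one week relative to the Interventions wording, and by longer where the community condition is the later date. The rule has to be in place before controls reach T1, because a T1 week recorded under access cannot be measured again.
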